#### 2.3.4. Inclusion Criteria

Premature babies born naturally or by caesarean section between 24 0/7 and 36 6/7 weeks of pregnancy.At least 24 h after the end of antibiotic therapy, if it is/was used.Up to 6 days of age OR up to 14 days of age in the case of transfer from another facility or temporary contraindications to the administration of microbiota (defined below).Newborns born in the hospital conducting the experiment and outside of it.Premature infants hospitalized in the intensive care unit and neonatal pathology unit during the study period.Signed informed consent of parents/legal guardians for the child’s participation in the experiment in the study group (with the administration of microbiota)—in the version for newborns born between 24 0/7 and 27 6/7 weeks of pregnancy.B. Signed informed consent of parents/legal guardians for the child’s participation in the experiment in the study group (with microbiota administration)—version for newborns born between 28 0/7 and 36 6/7 weeks of gestation.C. Signed informed consent of parents/legal guardians for the child’s participation in the experiment in the control group (without administration of microbiota)—in the version for the control group.

#### 2.3.5. Exclusion Criteria

Congenital defects of the digestive tract preventing normal intestinal transit (atresia of the esophagus, duodenum, rectum, tracheoesophageal fistula).The presence of genetic diseases diagnosed prenatally or perinatally (trisomy, other genetic syndromes).Active antibiotic therapy and the period up to 24 h after its completion.Perforation of the gastrointestinal tract.Food allergy with anaphylactic shock.Participation in another experiment or clinical trial that may affect the final outcome of the planned intervention.Lack of signed informed consent from parents/legal guardians for the child’s participation in the experiment in any of the three groups.

#### 2.3.6. Temporary Exclusion Criteria

Criteria for temporary postponement of microbiota administration (study group) and postponement of the matching time point for administration of intestinal microbiota doses (control group) if, prior to FMT or on day 6 of life, at least one of the following occurs as identical for microbiota administration and up to day 14 of life:Oral feeding intolerance: (assessed by the qualifying physician on the day of the planned FMT) if any of the following are present:
-Painful abdominal distension and/or visible intestinal loops.-Blood in the stool.-Increased gastric residuals:
Two consecutive episodes exceeding >50% of the volume of the previous portion.Two or more consecutive episodes of retention/bilious or duodenal residuals/emesis—when these episodes are not related to anxiety, delayed stool passage, the possibility of swallowing blood during delivery or from damaged nipples, incorrect positioning of the gastric catheter, bleeding from the nasal cavity.Increased gastric residual volume is not defined as a volume of up to 2 mL if the newborn receives a feeding portion of 1–2 mL.

Suspected NEC based on Bell’s criteria.Antibiotic therapy during planned FMT administration.Clinical/laboratory/radiological signs of infection—if at least one of the following clinical signs and/or more than one laboratory and/or radiological sign is present:
-Clinical symptoms of infection:
Hemodynamic instability: hypotension, tachycardia, peripheral circulation disorders (according to age norms), thermoregulation disorders, and fever > 38 °C, hypothermia < 36 °C.Apathy, lethargy, and convulsions.Apnea and deterioration of respiratory efficiency.
-Laboratory symptoms of infection:
Elevated inflammation parameters: leukocyte count< 5 and >30 thousand/μL up to 48 h and <5 and >20 thousand/μL > 48 h; left shift in neutrophil differential I:T > 0.2 for >34 h and >0.16 for <34 h.Platelet count < 50 K, coagulopathy.CRP > 0.05 mg/L (normal range < 0.05–1 mg/L); PCT (>72 h) > 0.5–1 ng/mL (normal range 0.5–1 ng/mL).Positive cultures of normally sterile body fluids.
-Radiological signs of infection, including systemic infection, e.g.,
Gallbladder bed edema.Unexplained pulmonary hypertension suddenly detected by echocardiography.

If any of the above-described temporary contraindications to FMT administration occur, the patient’s condition should be reassessed after a minimum of 6 h, and if the contraindications have resolved and do not recur within the next 6 h, the FMT procedure can be performed (in the study group) or a day identical to the day of microbiota administration (the so-called matching time point) can be set in the control group.

Assessment of the patient’s condition in terms of temporary contraindications to FMT administration and setting a date identical to the date of microbiota administration (the so-called matching time point):Physical examination.Follow-up laboratory tests:
-If CRP 0.06–1 mg/L and/or PCT 0.6–1 ng/mL, follow-up in 6–12 h; follow-up imaging tests in approx. 6–12 h.-In the case of a central culture collection, wait at least 24–48 h for the result.

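### A known, untreated, isolated positive sterile-site culture does not postpone FMT, because the infection rule counts it as one laboratory sign and requires more than one

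*Protocol article*

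**What the plan says.** All of the following is in the protocol article.

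- **Infection rule (2.3.6).** Administration is postponed "if at least one of the following clinical signs and/or more than one laboratory and/or radiological sign is present".
- **Where cultures sit (2.3.6).** "Positive cultures of normally sterile body fluids" is an entry under the laboratory signs, beside leukocyte and neutrophil criteria, platelets/coagulopathy, and CRP/procalcitonin. Nothing marks it as sufficient alone.
- **Clinical signs (2.3.6).** Fever above 38 °C is among them, and one clinical sign suffices.
- **Controls (2.3.6).** The same criteria govern "postponement of the matching time point for administration of intestinal microbiota doses (control group").
- **Antibiotics.** Section 2.3.5 excludes "Active antibiotic therapy and the period up to 24 h after its completion". Section 2.3.4 requires the same 24 h gap, and 2.3.6 postpones for antibiotics at the planned time of FMT.
- **Pending cultures (2.3.6, reassessment text).** "In the case of a central culture collection, wait at least 24–48 h for the result". The action on a positive result is not stated.
- **Release (2.3.6).** After reassessment at a minimum of 6 h, FMT may proceed "if the contraindications have resolved and do not recur within the next 6 h".
- **Second dose (4.3).** If a postponement criterion appears between the doses, the second may still be given when the criterion resolves within 6 h and stays away for a further 6 h.

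**The concern.** The rule is a safety gate for preterm infants, and staff are meant to apply it by counting signs. In that count, proof of organisms in a normally sterile site weighs the same as a mildly raised CRP and less than one fever reading. Staff told to wait for a culture result would, once a positive one arrives, find that the written rule does not tell them to hold the dose unless a second sign is present.

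Two things are at stake. The first is the infant: Section 4.3 names sepsis as the rare but dangerous complication to watch for after FMT. The second is interpretation. Section 4.3 counts infections and positive blood cultures over the next 72 h, and an infant dosed with a known positive culture blurs what was present beforehand and what is new. Section 4.1 also opens the 24 0/7 to 27 6/7 week phase only if no serious adverse event occurs, and that sentence makes no allowance for relatedness. An infection that predated dosing could therefore bear on that step.

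**Working it through.** The plan gives no figure to reproduce on this point, so the check is a truth table for the rule.

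**Inputs (2.3.6).** Let c, l and r be the numbers of clinical, laboratory and radiological signs. One clinical sign postpones. The phrase about laboratory and/or radiological signs can be read in three ways:

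- A, pooled: postpone if c ≥ 1 or l + r > 1.
- B, counted separately: postpone if c ≥ 1 or l > 1 or r > 1.
- C, more-than-one applies to laboratory signs only: postpone if c ≥ 1 or l > 1 or r ≥ 1.

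**Results.**

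| Findings | c / l / r | A | B | C |
|---|---|---|---|---|
| Positive culture only | 0 / 1 / 0 | no | no | no |
| Fever > 38 °C only | 1 / 0 / 0 | yes | yes | yes |
| Culture + CRP above cut-off | 0 / 2 / 0 | yes | yes | yes |
| Culture + any clinical sign | 1 / 1 / 0 | yes | yes | yes |
| Culture + one radiological sign | 0 / 1 / 1 | yes | no | yes |

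The first row is the finding: 1 is not more than 1, so no reading postpones.

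**Does another criterion catch the case?**

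1. Feeding intolerance, suspected NEC and the permanent exclusions in 2.3.5 do not mention cultures.
2. The antibiotic criteria in 2.3.4, 2.3.5 and 2.3.6 act only once treatment has begun.
3. The wait for a culture result ends when the result arrives. A positive result then goes back into the same count as one laboratory sign.

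**How often would a second sign be present?** Section 4.2 takes leukocyte count, CRP and procalcitonin before the first dose. The CRP entry is "CRP > 0.05 mg/L (normal range < 0.05–1 mg/L"), so the cut-off lies at the bottom of the printed normal range, and a value of 0.06 mg/L already supplies the second sign. The residual case is an infant with a positive culture, no antibiotics, no clinical sign and no other laboratory criterion met.

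**With the culture as a stand-alone trigger,** the first row changes to yes under every reading, and so does reading B in the last row. No row changes from yes to no.

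**The case against.** The strongest reply is that the residual case is nearly empty. A clinician who believes a positive sterile-site culture will treat it, and treatment postpones FMT. An untreated isolated positive in a well infant is plausibly one already judged a contaminant, and asking for corroboration of a laboratory result is defensible on that ground. Section 2.3.2 leaves administration to trained department physicians, and the criteria never compel infusion. The wait for a culture result also suggests that the authors meant a positive one to count.

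Most of this stands and limits the size of the point. It does not remove it. The rule does not separate a contaminant from a true positive: it lets both through uncounted, including in the interval between report and treatment. The wait shows a likely intention, but the action on a positive result is unwritten. Nor should the gate rely on the low CRP cut-off, since any upward revision of it would weaken that backstop.

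Five stronger readings are tempting but unsupported:

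- **That apnea alone outranks a positive culture.** The printed entry is "Apnea and deterioration of respiratory efficiency", joined by a conjunction, so read literally apnea alone need not count. Fever is the safer comparator.
- **That the 24–48 h wait fixes which cultures could report between the doses.** The wait is a minimum with no upper limit, and it is worded for a central culture collection. No such window can be derived.
- **That the wait contradicts the sign count.** It does not. It only leaves the next step unstated.
- **That FMT worsens an existing infection.** The documents do not say so.
- **That one amended sentence also settles the second dose.** Section 4.3 has its own condition of resolution within 6 h, which a culture result cannot meet in the ordinary sense.

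**Conclusion.** The point holds as a drafting gap in a stated safety rule. A known, untreated, isolated positive culture from a normally sterile site does not postpone FMT under any of the three readings, while one clinical sign such as fever above 38 °C does. It concerns what the printed rule says, not detail left to a fuller document.

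Its reach is small: treatment or a second laboratory sign will usually postpone FMT anyway. No effect on the planned comparisons is claimed. The conclusion rests on applying the sign count as printed and on each listed entry counting as one sign. It is worth changing because the change is cheap and protects infants, not because the trial is unsound without it.

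**What to change.** 1. **Rule (2.3.6).** Reword the threshold to: *at least one clinical sign, or a positive culture of a normally sterile body fluid, or more than one other laboratory and/or radiological sign*.
2. **Release for the first dose and the control matching time point (2.3.6).** A culture result does not resolve at a 6 h reassessment, so state the condition. Release comes 24 h after completed antibiotics if the infant is treated (matching 2.3.5), or once the physician documents the culture as a contaminant and the existing 6 h + 6 h checks are met. Both apply within the day-14 limit.
3. **Second dose (4.3).** State that a positive culture reported between the doses means the second dose is withheld, unless the culture is documented as a contaminant within the window that section already sets.

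**Cost.** One clause, one release condition and one sentence on the second dose, with no new sampling and no repeat culture. The downside is an occasional delay, or a missed second dose, for an infant whose culture proves to be a contaminant. Treated infants are already postponed by the antibiotic criteria.

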## 4. Detailed Procedure

### 4.1. Transplant Recipients Procedures

FMT will be administered to patients in the study group who meet the inclusion criteria and do not meet the exclusion criteria, in the form of a deep rectal infusion, in a volume of 5 mL, twice at 6 h intervals, between 3 and 6 days after birth and/or up to 14 days in patients who experience temporary contraindications to the use of FMT or in patients who will be transferred to our center for treatment from an external facility.

In the first phase of the experiment, 10 patients from the study group born between 28 0/7 and 36 6/7 will undergo the procedure. All adverse effects of the therapy will be monitored and documented on an ongoing basis. If no serious adverse events (SAEs) occur, we will include another 10 patients born between 24 0/7 and 27 6/7 in the study (phase two of the experiment).

A serious adverse event (SAE) is defined as any medical event that, at any dose, meets at least one of the following criteria:Leads to death.Is life-threatening to the participant.Requires hospitalization or prolongs hospitalization.Leads to permanent or significant impairment of function or disability.A detailed description of the monitored parameters is provided below.

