### 4.2. Protocol for Administering Fecal Microbiota Preparation

Check whether the patient is eligible for FMT therapy according to the inclusion criteria.Assessing possible contraindications to FMT therapy (according to the exclusion criteria).Discuss the therapy with the patient’s parents/guardians and obtain their consent for the child to participate in the experiment. Also obtain consent for the processing of personal data and the use of biological material samples for scientific purposes, as well as for participation in surveys and follow-up on the therapy’s effectiveness.Collection of blood inflammation parameters (leukocyte count, CRP and procalcitonin) at the “point 0” stage, i.e., before the administration of microbiota.Ensure that biological material samples are collected before (point “0”) FMT (feces, urine and blood samples), as described in the section below. Alternatively, collect samples before administering FMT.Familiarize yourself with the characteristics of producing donor intestinal microbiota preparations in the form of a suspension (MBiotix^®^ HBI; Warsaw, Poland) and with the procedure for administering the therapy to patients.Verify the presence of temporary contraindications to FMT administration.Obtain the FMT preparations from the storage location.Thaw the suspension in accordance with the characteristics of the FMT suspension production service and/or the manufacturer’s instructions. The suspension does not require special thawing conditions; allow the syringe to thaw in an uncovered container at an ambient temperature of 22–25 °C for approximately 2–2.5 h.Administer two doses of intestinal microbiota (FMT1 and FMT2).

Due to the high safety profile of this form of FMT administration, patients will receive the preparation via deep rectal infusion using a soft Foley catheter.

The catheter will be connected to a syringe containing the suspension, and its lumen will be filled with the suspension to minimize the risk of oxygen entering the intestinal lumen.

The Foley catheter will then be inserted into the rectum to a depth of approximately 10–15 cm. After placement, 5 mL of the preparation (from a syringe containing 8 mL of the suspension) will be slowly administered directly into the catheter. Ultrasound guidance will be used to confirm the correct position of the Foley catheter and ensure the preparation is administered to the correct location—the cecum area.

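### Section 2.3.6 prints a CRP sign of infection that contradicts its own normal range and a PCT sign with no single cut-off, so the decision to postpone FMT can differ between physicians

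*Protocol article*

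**What the plan says.** Section 2.3.6 of the protocol article postpones FMT in the study group, and the matching time point in controls, when infection is suspected. One clinical sign is enough. Without a clinical sign, the rule needs that "more than one laboratory and/or radiological sign is present".

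The laboratory list contains these two entries:

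- CRP: "CRP > 0.05 mg/L (normal range < 0.05–1 mg/L"
- PCT: "PCT (>72 h) > 0.5–1 ng/mL (normal range 0.5–1 ng/mL"

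The leukocyte limits depend on age. The wording "up to 48 h and <5 and >20 thousand" gives an upper limit of 20 thousand/µL after 48 h.

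The closing paragraphs of 2.3.6 add an instruction on repeat tests: "If CRP 0.06–1 mg/L and/or PCT 0.6–1 ng/mL, follow-up in 6–12 h". They also say when a postponement ends: the infant is "reassessed after a minimum of 6 h, and if the contraindications have resolved and do not recur within the next 6 h", and then FMT can be given or the control matching day set.

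Section 4.1 sets the outer limit for dosing, "up to 14 days in patients who experience temporary contraindications to the use of FMT". Section 4.2 lists "Collection of blood inflammation parameters (leukocyte count, CRP and procalcitonin" at point 0, ahead of the check for temporary contraindications.

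**The concern.** A postponement criterion should sort each value into sign or no sign. The CRP entry does this with one number, but the bracket beside it calls part of the same region normal. The PCT entry does not do it at all: an interval cannot serve as a greater-than limit, and this interval is also the stated normal range.

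The rule decides when a preterm infant with possible infection receives donor microbiota, and section 4.3 names sepsis as a rare but dangerous complication of the procedure. In the study group CRP and PCT are drawn before the first dose, so the values can be at hand when the decision is made. If two physicians read the limits differently, one doses an infant whom the other would postpone.

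**Working it through.** No sample size or power figure is involved. The check compares the printed intervals, counts signs under each reading, and then works out the timing.

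**Inputs (2.3.6 unless noted).** CRP sign above 0.05 mg/L, normal range reaching 1 mg/L. PCT sign and normal range both 0.5–1 ng/mL, for age over 72 h. Leukocyte sign above 20 thousand/µL after 48 h. Postpone without a clinical sign if the count of laboratory or radiological signs exceeds 1. Re-test in 6–12 h for CRP 0.06–1 or PCT 0.6–1. Six further hours without recurrence before dosing. Dosing from day 3 to day 6, at the latest day 14 (4.1).

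**Step 1: intervals.**

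- CRP above 0.05 and up to 1 is a sign by the cut-off and normal by the bracket. The span is 1 / 0.05 = 20-fold. If the bracket instead means that the upper limit of normal varies between 0.05 and 1, it still disagrees with a single cut-off of 0.05.
- PCT between 0.5 and 1 is a sign if the limit is 0.5. It is not a sign if the limit is 1 or if the normal range governs.
- The re-test bands start just above 0.05 and 0.5, which points to the lower figures as the working limits. PCT above 0.5 and below 0.6 falls outside the band and gets no action. This gap exists only if results carry more than one decimal place.

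**Step 2: counting signs.** Age over 72 h (3 days × 24 h = 72 h, so the 20 thousand leukocyte limit applies), no clinical or radiological sign.

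| Infant | Lower limits (0.05 and 0.5) | Upper figures (1 and 1) |
|---|---|---|
| CRP 0.03, leukocytes 22, PCT 0.8 | 1 + 1 = 2, postpone | 1, rule not met |
| CRP 0.5, PCT 0.8, nothing else, markers counted separately | 1 + 1 = 2, postpone | 0, rule not met |
| CRP 0.5, PCT 0.8, nothing else, markers counted as one sign | 1, rule not met | 0, rule not met |

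In the first row CRP lies below both printed figures, so the PCT reading alone changes the decision.

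**Step 3: timing for the first infant, if the first re-test is clear.**

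- PCT limit 0.5: (6 to 12) + 6 = 12 to 18 h until dosing is possible.
- PCT limit 1: 6 to 12 h if dosing is held for the re-test, 0 h if it is not.
- Difference: 6 h for the same re-test time, or 12 to 18 h if dosing is not held.

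**Step 4: upper bound.** If PCT stays at 0.8 and leukocytes stay above 20, the lower limit keeps postponing until day 14 at most: 14 − 6 = 8 days from day 6, or 14 − 3 = 11 days from day 3.

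**Reach.** For the second dose the limits matter only through an unscheduled test, since section 4.3 plans no CRP or PCT between doses. In controls the point-0 bloods are taken up to day 5 and the matching point is day 6 (4.4), so those values need not be the deciding ones.

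**The case against.** The strongest reply is that the section already resolves itself. The CRP criterion is one number and the bracket only a comment, so the CRP contrast arises only if a physician prefers the comment to the criterion. The re-test instruction sits under the assessment of temporary contraindications, and its lower ends agree with 0.05 and 0.5. Much of this stands. A reader might infer that PCT from 0.5 to 1 has no status anywhere in the plan; that goes too far, because 0.6–1 has a re-test. What remains is that a re-test is not a classification: the text does not say whether the value counts as a sign meanwhile.

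A second reply is that leukocytes, CRP and PCT may form one sign, since section 4.2 groups them as inflammation parameters and the list layout was lost in the extracted text. The first infant would then have one sign on either reading. As printed, however, the leukocyte item and the CRP/PCT item are separated by a full stop, and separate counting is the natural reading. If all three did form one sign, a platelet count below the listed 50 K limit could replace the leukocyte result, and the contrast returns.

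Two stronger readings should be set aside. One might suspect a wrong CRP unit, but both places in 2.3.6 use mg/L and nothing in the article points to an error. One might also infer that the primary endpoint is compromised, because section 5.1 counts rising inflammation indicators among adverse events and section 5.4 mentions CRP levels. The article does not say that the 2.3.6 limits define an adverse event.

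The value at which a sign has resolved may be set in the full protocol, which is not shown, so its absence here is not held against the plan.

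**Conclusion.** The inconsistency is real and stands in the current text. The CRP cut-off contradicts its normal range, and the PCT sign has no single cut-off. The re-test bands suggest the lower limits without settling whether values in the band count as signs.

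The severity is minor: a wording-level correction of a dosing threshold. The effect is on when FMT is given or the matching point set, usually by 6 to 18 h, with day 14 as the outer limit. At that limit it could decide whether an infant is dosed at all. It does not touch the endpoint definition or the analysis. The lower limits err towards delay, and the criteria are common to both groups.

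The examples assume separate counting of the listed items, no clinical sign, and, for the 6 to 18 h range, a clear first re-test. The article gives no CRP or PCT distribution, so the number of affected infants is unknown.

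**What to change.** Before enrolment, or before the next infant is assessed if enrolment has begun, correct section 2.3.6 as follows:

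1. Print one cut-off per marker: CRP above 0.05 mg/L and PCT above 0.5 ng/mL (age over 72 h), as the re-test bands imply, unless the clinical team states other values.
2. Let each normal range end at its cut-off.
3. Start the re-test bands at the same cut-offs, so that PCT between 0.5 and 0.6 is covered.
4. State that a value above the cut-off counts as a laboratory sign, and whether CRP and PCT count as one sign or two.

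The cost is a text correction and a note to the physicians who apply the rule. Design, sample size and analysis stay as they are.
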